### 2.6. Statistical Methods

The data will be analyzed using SPSS software, version 22. Initially, normality tests will be performed to assess the distribution, homogeneity, and comparability of the sample, employing kurtosis, skewness coefficients, and the Shapiro–Wilk test. A descriptive analysis will then be conducted using measures of central tendency and dispersion (SD) for quantitative variables, alongside calculations of the median and interquartile range (IQR). Qualitative variables will be expressed as frequencies (n) and percentages (%).

Subsequently, appropriate statistical tests will be conducted to determine whether the hypothesis can be rejected, analyzing relationships between the different variables. For qualitative variables, the Chi-square test will be used, or Fisher’s exact test if values < 5 are observed in the sample. For quantitative variables, Student’s t-test will be applied, or the Mann–Whitney U test in cases where the data do not follow a normal distribution.

In all calculations performed in the study, an alpha error of 0.05 and a beta error of 0.2 will be considered, with a 95% confidence level.

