### 2.5. Randomization of the Sample

Random assignment of participants to the Control Group (CG) and the Experimental Group (EG) will be conducted with a 1:1 ratio using a simple randomization method. Each participant will have an equal probability of being assigned to either group, minimizing bias and ensuring the equitable distribution of characteristics between the groups. To achieve this, a computer-generated random number sequence will be used. Additionally, random permuted blocks will be created to reduce the predictability of the random sequence, while ensuring an equal number of subjects in each group.

Those responsible for carrying out the techniques shall be unaware of the randomization code so that their performance is not constrained.

Details of the sample selection, inclusion criteria applied, and methods used for random assignments to CG and EG will be documented. This will ensure participants’ right to withdraw their data and guarantee the transparency and replicability of the study.

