## 4. Discussion

An extensive review of the literature was conducted to ensure this study protocol addresses current gaps in evidence, offering new insights into DIVA patient identification and the use of ultrasound-guided vascular access techniques in emergency departments (ED). This protocol integrates validated identification scales for DIVA, enhancing the reliability of patient categorization and improving clinical outcomes.

In ED settings, few studies have employed validated methods for identifying DIVA patients in conjunction with ultrasound-guided techniques from the outset. Most existing studies rely on subjective observations, such as palpable veins or the number of attempts required for successful venipuncture. Notable works, including those by Rodríguez-Herrera et al. [19] and Rubiera [34], have highlighted the potential of early identification in improving procedural success rates. The A-DICAVE scale, validated by [name] in 2020 [15,35], is among the few scales developed specifically for this purpose, yet its adoption in practice has been limited. To address this, our protocol incorporates the A-DICAVE scale to provide a standardized, objective approach for identifying DIVA patients.

Research comparing traditional and ultrasound-guided peripheral intravenous catheter (PIVC) insertion in EDs has consistently shown that ultrasound guidance improves first-attempt success and reduces the number of attempts required. Studies by Rubiera et al. [34] and Rodríguez-Herrera et al. [19] support these findings, yet these studies often lacked probabilistic sampling or failed to control for important variables like the use of medications through PIVCs. In contrast, our study accounts for such variables and includes confounding factors such as the cognitive state of patients, which may influence procedure outcomes.

Although patient satisfaction with ultrasound-guided techniques has been assessed in various studies [36], practitioner satisfaction remains underexplored. Given its impact on the adoption of new techniques in clinical practice, our protocol incorporates the evaluation of practitioner satisfaction as an additional key variable.

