Evidence supporting the benefits of ultrasound-guided PIVC insertion is robust, with a meta-analysis by Tran et al. [37] demonstrating a significant improvement in first-attempt success rates. However, these studies were not conducted in ED settings, highlighting the need for research tailored to the unique demands of EDs. Our protocol aims to fill this gap by focusing on ED populations, where challenges such as high patient turnover and time constraints are prevalent.

Regarding pain assessment, while tools like the Visual Analog Scale (VAS) have been used to measure discomfort, they typically exclude pediatric patients or those with cognitive impairments. To ensure a comprehensive evaluation, our study includes alternative pain assessment scales suitable for a broader patient population, including those with cognitive challenges.

The use of ultrasound for arterial punctures in EDs remains underexplored, with most research focused on critical care or anesthesia settings [38,39]. However, studies such as that by Grandpiere et al. [3] have demonstrated that ultrasound guidance reduces the number of attempts and associated pain in difficult arterial access cases. Our study builds on this evidence, extending its focus to include patients with cognitive impairments and healthcare professional satisfaction.

The benefits of ultrasound-guided techniques extend beyond clinical outcomes, leading to a reduction in resource usage. Fewer attempts reduce material consumption and optimize staff allocation, contributing to faster procedures, shorter ED stays, and quicker test results [6,11,40,41,42]. Additionally, the increased efficiency enhances healthcare professional satisfaction and improves overall workflow in EDs.

While this study may face limitations, such as the inability to implement a double-blind design, random sampling and data coding ensure the reliability of our findings. The single-center design could also limit generalizability; however, the protocol’s methodological rigor allows for adaptation to other centers, providing flexibility for future studies.

In summary, this study addresses critical gaps in the literature by incorporating validated DIVA identification scales and ultrasound-guided techniques for PIVC and arterial access in ED settings. By considering confounding variables and focusing on a representative patient sample, our research aims to provide valuable evidence to enhance ED practices and improve patient care.

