Secondary effects	Type of effects (extravasation, phlebitis, obstruction, others)
Patient satisfaction	Level of satisfaction (5-point Likert scale)
Family satisfaction	Level of satisfaction of the family (5-point Likert scale)
Professional satisfaction	Level of satisfaction of the professional who applied the technique (5-point Likert scale)
**Independent variables**	**Description**
Age	Years
Gender	Male, female, nonbinary
Reason for the consultation	Reason for the assistance according to nursing record
Emergency zone	Assigned emergency zone
Triage level	Classification SET (I, II, III, IV, V)
Predisposing factors of DIVA	Factors such as addiction, obesity, old age among others
**Procedure variables**	**Description**
Type of technique	Traditional, ultrasound guided
Transducer placement	Longitudinal, transversal, none
**Confusion variables**	**Description**
Medication given	Medication used through the access
Dilution volume	Volume in ml of the medication dilution
Time of administration	Taken time in minutes of the administration
Conscience level	Glasgow scale
Agitation	Yes/No

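### The Discussion says confounders are accounted for, but section 2.6 plans only unadjusted two-group tests, and three of the five listed confounders arise after cannulation

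*Protocol article*

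**What the plan says.** Section 2.6 names the tests. For categorical outcomes: "For qualitative variables, the Chi-square test will be used", with Fisher's exact test as the alternative when values below 5 occur. For quantitative outcomes: "For quantitative variables, Student’s t-test will be applied, or the Mann–Whitney U test in cases where the data do not follow a normal distribution". The section names no regression model, stratified method or covariate.

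The Discussion criticises earlier studies for not controlling for medication given through the catheter. It then sets this trial apart: "our study accounts for such variables and includes confounding factors such as the cognitive state of patients". Its closing summary repeats the point: "By considering confounding variables and focusing on a representative patient sample".

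Table 2 lists five variables under its confounder heading: medication given (described as "Medication used through the access"), dilution volume, time of administration, level of consciousness (Glasgow) and agitation. The difficulty-scale scores are filed under dependent variables. Age and predisposing factors are filed under independent variables. None is given an adjustment role.

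Section 2.5 says that allocation "will be conducted with a 1:1 ratio using a simple randomization method", and then that "random permuted blocks will be created to reduce the predictability of the random sequence".

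**The concern.** Two statements in one document do not fit together. Control of confounders is presented as an advantage over earlier work, yet no test in the analysis section can deliver it.

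The list of confounders is also mostly the wrong one. In a randomised comparison, the variables worth adjusting for are measured before the puncture and predict the outcome. The trial already collects such variables: the scale score that decides PIVC eligibility, age and predisposing factors, plus Glasgow and agitation if recorded beforehand. Three of the five variables actually labelled as confounders come after cannulation.

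At stake is precision in a small trial that mixes children and adults scored on different scales, and a claim in the Discussion that the analysis would not support.

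**Working it through.** **1. Claim against method**

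| Source | Content |
|---|---|
| Discussion | Medication through the catheter is accounted for; cognitive state is included as a confounder |
| Section 2.6 | Chi-square/Fisher; t/Mann–Whitney. No covariate enters any of them |

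**2. When each listed confounder arises**

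| Table 2 variable | Timing |
|---|---|
| Medication given | After a working access |
| Dilution volume | After a working access |
| Time of administration | After a working access |
| Glasgow | Can be baseline; timing not stated |
| Agitation | Can be baseline; timing not stated |

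The first three follow the outcomes of success, attempts, procedure time and procedural pain, so they cannot confound the effect of allocation on them.

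**3. The plan's own sample-size figure (section 2.4)**

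Inputs: difference 0.52 and variance 1.64 (section 2.4); alpha 0.05 and beta 0.2 (section 2.6); two-sided testing assumed.

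n per arm = 2 × 1.64 × (1.960 + 0.842)² / 0.52² = 95.2

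The stated 95 therefore matches a per-arm number, but the plan uses it as the total (95 × 1.2 = 114, or 57 per arm). That is a separate error. It matters here only because it sets the starting power.

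**4. Power with and without baseline adjustment**

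Let R² be the share of within-arm variance in attempts explained by baseline covariates. The documents give no value, so 0.1–0.2 is an assumption.

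- Residual variance = 1.64 × (1 − R²)
- SE = √(2 × residual variance / n per arm)
- Noncentrality = 0.52 / SE
- Power from the noncentral t distribution with 2n − 2 degrees of freedom, two-sided 0.05, ignoring the few degrees of freedom spent on covariates

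| n per arm | R² | Residual variance | SE | 0.52/SE | Power |
|---|---|---|---|---|---|
| 57 (all 114) | 0 | 1.640 | 0.240 | 2.17 | 57.5% |
| 57 | 0.1 | 1.476 | 0.228 | 2.28 | 62.0% |
| 57 | 0.2 | 1.312 | 0.215 | 2.42 | 67.1% |
| 47.5 (95 evaluable) | 0 | 1.640 | 0.263 | 1.98 | 49.9% |
| 47.5 | 0.1 | 1.476 | 0.249 | 2.09 | 54.2% |
| 47.5 | 0.2 | 1.312 | 0.235 | 2.21 | 59.1% |

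In patient numbers, 114 / 0.9 = 127 and 114 / 0.8 = 142.5, so the gain is equivalent to about 13 to 28 extra patients. At 95 evaluable, R² would have to be about 0.5 before power came close to 80%.

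**5. Illustration of adjusting for a consequence of the outcome**

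A simulation of 1,000,000 patients with a true difference of −0.52 gave −0.52 after adjustment for a baseline variable. After adjustment for a variable caused by the outcome, it gave about −0.47 (correlation with the outcome about −0.31) or −0.37 (about −0.55). The correlations are invented. They show the direction of the risk, not its size in this trial.

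**The case against.** The strongest reply is that covariate models are commonly left to an analysis plan, which is not shown, and that unadjusted tests are valid under 1:1 randomisation. Both points stand. A missing model alone would not be a finding. What remains is that the Discussion claims something section 2.6 does not provide, and that variables are labelled confounders when they cannot be.

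A reader might infer stronger things that the documents do not support:

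- **That the planned comparison is biased.** It is not. Randomisation protects it, and only precision is lost.
- **That a harmful adjustment is planned.** No section enters any of the five variables in a model. The shrinkage illustrated above would occur only if someone later used the post-cannulation variables as covariates. Medication and volume are also natural descriptors for catheter permanence, phlebitis and extravasation, which Table 2 lists as outcomes.
- **That adjusting for medication would drop every failed patient.** A patient whose first attempt fails but who is cannulated later can still have medication data. Patients never cannulated, or given no drug, would be lost.
- **That the power gain is assured.** PIVC patients enter only with A-DICAVE 3–5 or DIVA of at least 4. This restricted range weakens the score as a predictor, and the gain could be close to nil.

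On randomisation, the reference to blocks and equal group sizes suggests that blocking is intended. The absence of strata is not an error.

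**Conclusion.** The point holds as an internal contradiction with a modest, uncertain cost. The Discussion's claim has no counterpart in section 2.6, and three of the five listed confounders cannot confound the procedural outcomes.

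The cost is roughly 4 to 10 percentage points of power for number of attempts, the variable on which the PIVC cohort was sized. This rests on an assumed R² of 0.1–0.2, two-sided alpha of 0.05, and the plan's own difference and variance. It may be near zero. It does not make up for the per-arm number having been used as a total.

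The mixed wording on simple and permuted-block randomisation is a secondary point that needs one clear statement.

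**What to change.** 1. **PIVC.** Make the main analysis of attempts a linear model with robust standard errors on allocated arm, age group (<14/≥14) and baseline score. Standardise the score within its own scale or give each scale its own slope, because A-DICAVE (0–5) and DIVA (0–10) cannot share one.
2. **ABG.** Estimate the risk difference in first-attempt success, adjusted for age and Glasgow recorded before puncture.
3. **Post-cannulation variables.** State that medication, dilution volume and administration time are not adjusted for in success, attempts, time or pain. Keep them only as descriptors for later outcomes such as permanence and phlebitis.
4. **Discussion.** Amend both statements on confounders to describe what the analysis will do.
5. **Section 2.5.** Delete the reference to simple randomisation and keep permuted blocks, with a separate list for each cohort (PIVC and ABG).

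Cost: changes of wording and two computer-generated lists. No new variable is needed. The data form must make clear that Glasgow is taken before the puncture.

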### 2.4. Sample Size

The sample size calculation will be based on the minimum sample size formula for mean comparison. Considering data from a similar study conducted in other healthcare settings [6] and assuming a minimal detectable mean difference of 0.52 and a variance of 1.64 (“number of attempts” variable), a minimum sample size of 95 participants was obtained. Accounting for a 20% loss rate, the required sample size increases to 114 participants, with 57 in each group.

For the sample size required for arterial puncture, the calculation will follow data from a study by Grandpiere et al. [3], which reported a 34% difference in success rates using ultrasound compared to the traditional technique. To demonstrate a minimum difference of 37% in the first-attempt success rates between the two groups, with an alpha error of 0.5%, 90% power, and accounting for a 20% loss rate, the required sample size is 80 participants, with 40 in each group.

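### The venous comparison is sized on a difference in mean attempts, but a normality check decides whether means or ranks are tested, and attempt counts will almost surely fail it

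*Protocol article*

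**What the plan says.** Section 2.4 (Sample Size) states: "The sample size calculation will be based on the minimum sample size formula for mean comparison". For the number of attempts it proceeds by "assuming a minimal detectable mean difference of 0.52 and a variance of 1.64", and "a minimum sample size of 95 participants was obtained".

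Section 2.6 (Statistical Methods) first assesses the distribution by kurtosis, skewness and Shapiro–Wilk. Quantitative variables then get Student's t-test, or the Mann–Whitney "U test in cases where the data do not follow a normal distribution". No cut-off is given for any of the three checks, none takes priority, and number of attempts is not exempted.

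For qualitative variables the section uses chi-square, or Fisher's "exact test if values < 5 are observed in the sample".

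The error rates are common to everything: "In all calculations performed in the study, an alpha error of 0.05 and a beta error of 0.2 will be considered". Table 2 defines number of attempts as a count of punctures and lists it among many dependent variables. No outcome is singled out as carrying the conclusion, although section 2.4 sizes on two: attempts for PIVC and first-attempt success for arterial puncture.

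**The concern.** A sample size calculation and the main analysis should address the same quantity. Here the calculation concerns a difference in means, while the analysis depends on the outcome of a preliminary check. For a count that takes mostly the values 1, 2, 3 and a few more, that check has a nearly certain result, so the test that was powered is not the one likely to be run.

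Mann–Whitney compares the ordering of two distributions. Its null hypothesis is not equality of means, and it yields no confidence interval for the difference in mean attempts. A reader who wants to know whether ultrasound saves about half a puncture per patient would have a P value for a different question.

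The missing decision rule adds a second problem. If the three checks disagree, the analyst can choose between two tests after seeing the data.

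The Fisher trigger is a smaller fault of the same kind: a rule for choosing a test that looks at the wrong quantity. The chi-square approximation depends on expected cell counts, not observed ones.

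**Working it through.** **Inputs.** From section 2.4: difference 0.52, variance 1.64 (SD √1.64 = 1.281), 95 before losses, 114 after a 20% allowance (57 per group), and 40 per group for arterial puncture. From section 2.6: alpha 0.05, beta 0.2. Two-sided testing is assumed, since sidedness is not stated. Distributions and control means for attempts, and success rates for arterial puncture, are not in the document and are assumed below.

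**1. The plan's figure.** The formula for two means is n per arm = 2(z₀.₉₇₅ + z₀.₈₀)² × variance / difference² = 2 × (1.960 + 0.842)² × 1.64 / 0.52² = 95.2. So the figure 95 does come from a two-mean, t-type calculation. It comes out as a number per arm, whereas the article uses it as a total. That is a separate matter, but it sets the baseline: with variance 1.64 in both arms, t-test power is about 58% at 57 per arm and 51% at 47.5 per arm (95 / 2).

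**2. Does the normality check have a foreseeable result?** Integer attempt counts were simulated, 3,000 trials per scenario, with Shapiro–Wilk at 0.05 in each arm and rejection in either arm counted as non-normal. At 47 per arm it rejected in 99.7% of trials for rounded normal data and in 100% for every other shape. At 57 per arm it rejected in 100% throughout. Choosing the test by Shapiro–Wilk therefore gave the same power as always using Mann–Whitney.

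**3. What does the switch do to power?** Mean difference 0.52, 57 per arm, two-sided 0.05; simulation error is about 1 percentage point (√(0.25/3000) = 0.9).

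| Assumed distribution of attempts | Means | Student's t | Mann–Whitney |
|---|---|---|---|
| 1 + negative binomial, variance about 1.64 in both arms | 2.0 vs 1.48 | 60.8% | 93.1% |
| 1 + negative binomial, variance about 1.64 in both arms | 2.5 vs 1.98 | 58.4% | 75.5% |
| 1 + negative binomial, variances 2.0 and 1.64 | 3.0 vs 2.48 | 53.4% | 55.1% |
| 1 + Poisson, variances 1.51 and 0.98 | 2.5 vs 1.98 | 69.1% | 66.4% |
| Rounded normal | 4.0 vs 3.48 | 56.0% | 53.7% |
| Geometric, variances 2.0 and 0.71 | 2.0 vs 1.48 | 69.9% | 60.8% |
| 1 + negative binomial, variances 2.3 and 0.97 | 2.5 vs 1.98 | 60.2% | 40.5% |

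The mean difference is the same in every row, yet Mann–Whitney power runs from 40.5% to 93.1%. The rank test responds to features of the distribution that section 2.4 does not specify.

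**4. The Fisher trigger.** Forty per arm less 20% leaves 32. Take assumed success rates of 55% and 92%, which differ by the 37 points of section 2.4. Failures average 0.08 × 32 = 2.6 in the ultrasound arm, so an observed cell below 5 is usual. The expected number of failures per arm averages (14.4 + 2.56) / 2 = 8.5, so an expected count below 5 is rare. Enumerating all tables exactly:

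- an observed count is below 5, and Fisher is used, in 89% of datasets;
- an expected count is below 5 in 0.8%;
- power is 92.7% under the rule as written and 94.9% under an expected-count rule, a difference of 2.2 points.

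**The case against.** **The rank test need not lose power.** A reader might infer that the switch to Mann–Whitney weakens the trial. The documents do not support that. With variance near 1.64 in both arms and right-skewed counts, Mann–Whitney does as well or better, in some cases by a wide margin. It loses where the ultrasound arm also has a clearly smaller variance, and slightly for Poisson or rounded normal counts. Without a stated distribution or control mean, the direction is undetermined. This objection stands; the finding is about what is tested, not about a loss of power.

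**The text does not say that Mann–Whitney will always be used.** Shapiro–Wilk is one of three checks and is not named as decisive. This also stands: the switch is almost sure if Shapiro–Wilk decides, but the wording leaves room for another outcome. That room is itself part of the problem.

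**The means will still be described.** Section 2.6 promises central tendency and SD for quantitative variables, so arm means should appear in the report. What is missing is a test of their difference and a confidence interval for it.

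**Fisher's test is valid at any count.** True. The observed-count trigger does not inflate the type I error. It only gives up a little power, and the phrase may be loose wording for expected counts.

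**A reader might go further and put a figure on false positives across the many variables in Table 2.** Such a figure would require independence, and success, attempts, nurses attempting and time overlap heavily. The documents do not support a number.

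**Details may sit in a fuller plan.** That would excuse silence. Here the article states a rule for choosing the test, and it is the stated rule that conflicts with section 2.4.

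**Conclusion.** The concern holds as a mismatch between the sized quantity and the likely test, made worse by a test choice that depends on the data and has no decision rule. Number of attempts would fail Shapiro–Wilk almost surely (99.7% to 100% of simulated trials), so the outcome sized on a mean difference of 0.52 would be analysed by a rank test that does not address that difference. The effect on power is unknown in direction: at 57 per arm the gap between Mann–Whitney and t ran from about 20 points lower to 32 points higher across the assumed shapes.

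The near-certain rejection rests only on attempts being small integers and held for every shape tried. The power figures rest on assumed distributions and control means. The Fisher trigger is misstated but minor: about 2 points of power at assumed rates of 55% and 92% with 32 per arm.

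This should be corrected before analysis. It does not invalidate the design.

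**What to change.** In section 2.6:

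1. Remove the normality check as a selector for number of attempts. Fix in advance one analysis that matches section 2.4: the difference in mean attempts with a 95% confidence interval, by Welch's t-test or by linear regression with robust standard errors. Keep Mann–Whitney as a sensitivity analysis.
2. Change the Fisher trigger from observed values below 5 to expected counts below 5.
3. State that the two sized outcomes, number of attempts for PIVC and first-attempt success for arterial puncture, carry the main conclusions, and that the remaining variables are supportive.

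The cost is a few sentences. There are two downsides. For some skewed shapes the comparison of means has less power than the rank test (60.8% against 93.1% in the most extreme case above). The other outcomes also lose any confirmatory standing. If the sponsor prefers the rank test as the main analysis, the alternative is to say so and size the trial on it, which requires stating an assumed distribution of attempts in each arm.
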